# Effect of the clinical decision assessment system on clinical outcomes of delirium in hospitalized older adults: study protocol for a pair-matched, parallel, cluster randomized controlled superiority trial

**DOI:** 10.1186/s13063-023-07607-3

**Published:** 2023-09-11

**Keywords:** Delirium, Older adults, Clinical outcome, Clinical decision assessment system, Protocol

## Abstract

**Background:**

Prompt recognition of delirium is the first key step in its proper management. A previous study has demonstrated that nurses’ delirium screening using the usual paper version assessment tool has no effect on clinical outcomes. Clinical decision assessment systems have been demonstrated to improve patients’ adherence and clinical outcomes. Therefore, We developed a clinical decision assessment system (3D-DST) based on the usual paper version (3-min diagnostic interview for CAM-defined delirium), which was developed for assessing delirium in older adults with high usability and accuracy. However, no high quality evidence exists on the effectiveness of a 3D-DST in improving outcomes of older adults compared to the usual paper version.

**Methods:**

A pair-matched, open-label, parallel, cluster randomized controlled superiority trial following the SPIRIT checklist. Older patients aged 65 years or older admitted to four medical wards of a geriatric hospital will be invited to participate in the study. Prior to the study, delirium prevention and treatment interventions will be delivered to nurses in both the intervention and control groups. The nurses in the intervention group will perform routine delirium assessments on the included older patients with 3D-DST, while the nurses in the control group will perform daily delirium assessments with the usual paper version. Enrolled patients will be assessed twice daily for delirium by a nurse researcher using 3D-DST. The primary outcome is delirium duration. The secondary outcomes are delirium severity, incidence of delirium, length of stay, in-hospital mortality, adherence to delirium assessment, prevention, and treatment of medical staff.

**Discussion:**

This study will incorporate the 3D-DST into clinical practice for delirium assessment. If our study will demonstrate that 3D-DST will improve adherence with delirium assessment and clinical outcomes in older patients, it will provide important evidence for the management of delirium in the future.

**Trial registration:**

Chinese Clinical Trial Registry, Identifier: ChiCTR1900028402. https://www.chictr.org.cn/showproj.aspx?proj=47127. Protocol version: 1, 29/7/22.

**Supplementary Information:**

The online version contains supplementary material available at 10.1186/s13063-023-07607-3.

## What is already known

Delirium screening using the usual paper version assessment tool by nurses has no effect on clinical outcomes.Clinical decision assessment systems have been demonstrated to improve patients’ adherence and clinical outcomes.No high-quality evidence exists on the effectiveness of a 3D-DST in improving outcomes of older adults compared to the usual paper version.

## What this paper adds

A cluster randomized controlled trial will be conducted to evaluate the effect of the 3D-DST on clinical outcomes.Findings will improve policy and practice for delirium management.

## Introduction

Delirium is a common neurocognitive syndrome in hospitalized older adults with fluctuating symptoms [1, 2]. The incidence of delirium in hospitalized older adults has been reported to be 10% ~ 40% in different settings [3–6]. Delirium during hospitalization will increase the risk of falls, decrease cognitive function, aggravate frailty, and increase mortality in older adults [1, 7]. The severity of adverse effects was positively correlated with the severity and duration of delirium [8]. Prompt recognition of delirium is the first key step in its proper management.

Relevant guidelines for the routine assessment and management of delirium have been issued [9, 10], and several studies have found that delirium assessment combined with multi-component intervention can effectively improve clinical outcomes of patients [11, 12]. However, the majority of patients are not routinely monitored for delirium, guidelines are poorly implemented and hindering timely prevention and management [13]. The possible reasons for the low adherence to delirium assessment are multiple but mainly due to the implementation barriers, such as the monitoring instrument is not routinely used, the complicated procedure of the evaluation instrument, the long evaluation time required for delirium increases the workload of the nurse, etc. [14–16]. A prospective study also demonstrates that routine delirium detection by bedside nurses using the usual paper version assessment tool does not improve clinical outcomes [17].

Clinical decision assessment systems have been widely used in the medical field and have been demonstrated to improve patients’ adherence and clinical outcomes [18, 19]. We have developed a clinical decision assessment system (3D-DST) based on the 3-min diagnostic interview for CAM-defined delirium (3D-CAM), which is developed for the assessment of delirium in older adults with high sensitivity and specificity [20]. 3D-DST simplified the evaluation process of the 3D-CAM paper version, the usability of 3D-DST is significantly better than that of the paper version when used by bedside nurses, and the assessment time has been shortened by 2.1 min [20]. However, no high quality evidence exists on the effectiveness of 3D-DST in improving delirium identification and clinical outcomes of older adults compared to the usual paper version.

Therefore, we hypothesize that the use of the 3D-DST will improve the adherence to delirium assessment and management by clinical staff, and reduce the duration and the severity of delirium.

## Objectives

The primary objective is to determine the effect of routine delirium assessment using the 3D-DST by bedside nurses on the duration of delirium.

The secondary objectives are to determine the impact of routine delirium assessment using the 3D-DST by bedside nurses on delirium severity, incidence, length of stay, in-hospital mortality, adherence to delirium assessment, prevention, and treatment of medical staff.

## Methods

### Reporting guideline

Following the defining standard protocol items for clinical trials (SPIRIT 2013) [21]. SPIRIT Checklist is included as Additional file 1 and the SPIRIT Figure is shown in Fig. 1.

**Fig. 1 Fig1:**
[figure not shown]
Schedule for enrolment, data collection, assessments, interventions and outcome measures

### Design and setting

This study is a pair-matched, open-label, parallel, cluster randomized controlled superiority trial with a 1:1 allocation ratio. Cluster randomization minimizes group contamination and accounts for intraclass correlation [22]. Four medical wards (two respiratory and two neurology wards) of a geriatric hospital in China will be invited to participate in the study. The neurology and respiratory wards receive approximately 20 and 40 older adults per month, respectively. This study was registered on the Chinese Clinical Trial Registry (registration number: ChiCTR1900028402).

### Participants

The participants are older patients continuously admitted to four general medical wards. Patients should be: 1) age ≥ 65 years old, 2) able to communicate effectively in Mandarin, 3) stay in the hospital longer than two days. Exclusion criteria are: 1) severe hearing or visual impairment, 2) refuse to participate in this study, 3) continuous coma during the study period, 4) severe dementia which is defined as a diagnosis documented in the medical record because such patients cannot be assessed for delirium. This study was approved by the ethics committee of the Capital Medical University and the study hospital. Patients who meet the inclusion criteria will be informed about the study protocol, and written informed consent will be obtained from the older participant or their legal representatives by the first author. Three supervisors (member of the Ethics Committee, administrators of the research program and education department in the hospital) will monitor the accuracy and feasibility of the research process once a year.

### Instruments for delirium assessment

#### 3D-CAM paper version

A total of 22 items and four features are included in the 3D-CAM assessment. Four features are acute change and fluctuation of mental status (feature one), inattention (feature two), disorganized thinking (feature three), and altered level of consciousness (feature four) [23]. Delirium is positive if feature one and feature two are present with either feature three or feature four. The 3D-CAM has been translated into Chinese [24]. Previous evidence has shown highly acceptable sensitivity and specificity of 3D-CAM for routine delirium assessment when used by nurse researchers [24].

#### 3D-DST

Based on the paper version, the 3D-DST was programed to fit on Android-compatible smartphones through three steps include analysis of problems in the use of the 3D-CAM, design of the 3D-DST (evaluation process analysis and optimization, and user interface design), architecture and development of 3D-DST [25]. A multidisciplinary team that included experts with rich experience in delirium assessment, bedside nurses, nurse researchers, software engineers and user interface designers were formulated to develop the 3D-DST. Three assessment modules (inquiry assessment, observation assessment and selective assessment), nine assessment interfaces with built-in reminders to guide nurses to complete the assessment, and 16 result interfaces were included in the final 3D-DST version (Fig. 2) [20]. The 3D-DST final version has fully addressed the problems that were identified when using the 3D-CAM by bedside nurses, including human error, incorrect understanding of the item content, and incomplete nursing records when the 3D-CAM was used by nurses. In the usability testing, a total of 432 delirium assessments on 148 older adults were performed by 72 bedside nurses [25]. Our previous research had shown that the 3D-DST had good usability when used by bedside nurses, reduced human error, and saved evaluation time compared to the paper version (2.3 min vs. 4.4 min) [25].

**Fig. 2 Fig2:**
[figure not shown]
Interfaces of the 3D-DST

#### CAM-S

Inouye et al. have developed a delirium severity scoring system (CAM-S) [26]. CAM-S can only be used to assess the severity of delirium and not be used to diagnose delirium. The simple version of CAM-S includes the following items: acute episodes or symptom fluctuations, impaired attention, incoherent thinking, and changes in consciousness. The results show that the overall agreement of the CAM-S scale is 97%. The score range is 0 to 7 ( 0 = normal, 1 = mild delirium, 2 = moderate delirium, and 3–7 = severe delirium [26]. The CAM-S has been translated into Chinese with high reliability and validity and can be used as an effective tool to evaluate the severity of delirium [27].

### Cluster randomization and blinding

Before randomization, the wards that participated in the study will be pair matched according to the specialty. Within each of the two pairs, wards will be randomly assigned (1:1) to the intervention or control group using random numbers generated by the computer, which indicates that each group will contain one neurology and one respiratory ward. The medical staff who will be involved in the study only know the protocol of their ward, but not be aware of the protocol of other wards and the hypothesis of the study. Due to the allocation sequence generating, participants’ enrollment, participants’ assignment, data and outcome collection will be done by a nurse researcher, therefore the protocol will not be blinded to the nurse researcher. However, the nurse researcher and the bedside nurse will be unaware of each other's assessment results of delirium.

### Sample size

The primary outcome is delirium duration. We expect that the delirium duration of the intervention group will be one day shorter than that of the control group, with a standard deviation of 1.8 [28], α of 0.05, and intraclass correlation coefficient of 0.00001. Our study will be estimated to provide more than 80% power, at least five delirium-positive patients in each group (ward), and 20 delirium-negative patients will be needed. According to our previous study, the incidence of delirium is approximately 10%, with an estimated 10% of patients dropping out during the study, at least 202 older patients will be needed. Patients will be given a detailed explanation of the benefits they will receive from participating in the study to reach the target sample size.

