### Statistical analysis

SPSS 22.0 (SPSS Inc., Chicago, Illinois, USA) will be used for statistical analysis. Multiple imputation will be used to fill in missing data using the R software. A *P*-value of 0.05 will be defined as statistically significant. The continuous data will be tested for normality and homogeneity of variance by the "One-Sample Kolmogorov Smirnov Test" and the "Homogeneity of Variance Test". Mean and standard deviation (SD) will be used for normally distributed continuous variables, median and interquartile range (IQR) will be used for continuous variables with non-normal distribution. The rank sum test and *t*-test will be used to compare the demographics and clinical characteristics of different groups. Categorical variables will be expressed in frequency and percentage, and the Chi-square test or Fisher's Exact Test will be used for comparing variables between different groups. The effects on clinical outcomes will be analyzed by a generalized linear mixed model. Subgroup analysis will be performed to eliminate the effect of confounding factors (age, gender, education level, comorbidity, marital status, smoking, drinking, cognitive function, physical function, depression, and comorbidity). Data will be analyzed according to the per-protocol principle. The preliminary analysis will be conducted after the start of the study (three months, one year, close-out).

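### An ICC of 0.00001 removes clustering from the sample size, and with four wards in two pairs the claimed power above 80% is not available at ward level

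*Protocol article*

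**What the plan says.** The Sample size section expects that delirium duration in the intervention group "will be one day shorter than that of the control group", "with a standard deviation of 1.8", and adds "α of 0.05, and intraclass correlation coefficient of 0.00001". It claims more than 80% power, asks for at least five delirium-positive and 20 delirium-negative patients per ward, and arrives at 202 patients. The standard deviation carries a citation; the ICC does not.

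Design and setting fixes four wards, two respiratory and two neurology, calls the study a superiority trial, and states: "Cluster randomization minimizes group contamination and accounts for intraclass correlation". Cluster randomization and blinding allocates wards within two specialty-matched pairs, "which indicates that each group will contain one neurology and one respiratory ward".

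Under Statistical analysis, "The effects on clinical outcomes will be analyzed by a generalized linear mixed model", and the threshold is a P-"value of 0.05 will be defined as statistically significant".

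The limitations paragraph of the Discussion names the single hospital and the open-label design, but not the number of wards.

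**The concern.** The intervention works through nurses who are trained for their ward's tool and use that tool on all included patients. Patients in one ward therefore share staff, routines and discharge practice. Some correlation within wards is what one would expect, and the plan assumes essentially none.

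The Design and setting sentence has the logic reversed. Randomising wards is what makes the intraclass correlation matter; the sample size and the analysis have to account for it.

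With two wards per arm, a difference between particular wards that matching on specialty does not remove could be credited to 3D-DST, and a patient-level standard error would give no warning of it.

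**Working it through.** **Inputs.** From Sample size: difference 1 day, SD 1.8, α 0.05 (taken as two-sided; the article does not say), ICC 0.00001, total 202. From Design and setting and Cluster randomization and blinding: four wards, two pairs, two wards per arm. Ward sizes m: 5 (positives only), 25 (5 + 20), and 50.5 (202/4). Equal ward sizes are assumed, although the article gives unequal monthly admissions. ICCs of 0.01 to 0.05 are assumptions; the article offers no alternative value.

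**1. The plan's own figure.** Treating patients as independent, n per arm = 2(1.96 + 0.84)² × 1.8² / 1² ≈ 51, so 102 in total, or 114 after 10% dropout. Four wards of 25 give 50 per arm and 79.3% power; 101 per arm gives 97.7%. Ten positives per arm give only 24%. The 202 does not follow from these inputs, which is a separate matter. What counts here is that about 80% or more is reached only by counting all patients as independent.

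**2. Design effect.** DE = 1 + (m − 1) × ICC.
- Stated ICC, m = 50.5: 1 + 49.5 × 0.00001 = 1.0005.
- ICC 0.01: 1.495. ICC 0.05: 3.475.
- As m grows, the effective number per arm cannot exceed 2/ICC. At ICC 0.05 that is 40, below the 51 required, however many patients are recruited.

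**3. Randomisation test.** Two pairs give 2² = 4 allocations. The smallest two-sided p is 2/4 = 0.5 (one-sided 0.25).

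**4. Ward-level t-test.** With two wards per arm, SE = 1.8 × √[ICC + (1 − ICC)/m]. Critical values are 4.30 on 2 df and 12.71 on 1 df (pairs kept). Power is from the noncentral t with noncentrality 1/SE. The same SE is used for both tests, so pairing is assumed to remove no variance.

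| m | ICC | SE | Power, 2 df | Power, 1 df |
|---|---|---|---|---|
| 5 | 0.00001 | 0.805 | 12% | 8% |
| 25 | 0.00001 | 0.360 | 35% | 17% |
| 50.5 | 0.00001 | 0.253 | 56% | 24% |
| 50.5 | 0.01 | 0.310 | 43% | 20% |
| 50.5 | 0.05 | 0.472 | 24% | 13% |

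**5. Type I error of an uncorrected mixed model.** Simulated null trials (200,000 per setting): four equal wards, normal outcome, random ward effect, REML with the variance truncated at zero, Wald z-test. Ranges cover models without and with pair as a fixed effect.

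| m | ICC | Mixed model, Wald | Wards ignored |
|---|---|---|---|
| 50 | 0.00001 | 3.9% | 5% |
| 50 | 0.01 | 7–8% | 11% |
| 50 | 0.05 | 14–17% | 29% |
| 5 | 0.01 | 5–6% | 5–6% |
| 5 | 0.05 | 7% | 7% |

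At m = 50, over ICCs from 0.00001 to 0.05, the ward variance was estimated as exactly zero in 24% to 68% of runs.

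**The case against.** The strongest reply is that the article only condenses a fuller plan. Random effects, the pair term and the degrees-of-freedom method may be set out there, and their absence here is no finding. That stands. The point rests on what the article does fix: the ICC, the power claim, the four wards and the sentence on intraclass correlation.

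Four stronger readings are tempting, and the documents do not support them.

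- A reader might infer that no valid 5% test exists. That is true only of the randomisation test. A ward-level t-test holds its level under normality; what it lacks is power.
- A reader might infer that the intervals will be too narrow. That needs a material true ICC and no small-sample correction. At the stated ICC the Wald test rejects a true null 3.9% of the time, and in the same simulation with 50 per ward its power for one day is 91%. If the ICC really were that small, the claim could be met in an all-patient analysis.
- A reader might infer that a mixed model with four wards falls back on patient-level precision. The variance often collapses to zero, but not always, and the simulated error lies between the nominal level and that of ignoring wards.
- A reader might blame clustering for the whole shortfall at five positives per ward. Most of it is patient numbers: power is about 24% even with independent patients.

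It is also fair to say that matching on specialty balances part of the case mix, and that the limitations paragraph calls the conclusions a preliminary basis. Against that, the Discussion also says the design can give strong evidence.

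**Conclusion.** The concern holds in this limited form. The ICC of 0.00001 is in effect an assumption of no clustering, given without a basis, in a trial that randomises four wards. Power above 80% at 0.05 holds at best if patients are treated as independent. At ward level and at the plan's own ICC it is 56% or 24% (2 or 1 df) with about 50 patients per ward, if duration is analysed in all patients, and 12% or 8% with five positives per ward.

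Inflated type I error is conditional on a true ICC of the assumed order of 0.01 to 0.05 and an uncorrected mixed model. It is then 7–8% to 14–17% at 50 per ward, small at five per ward (5–7%), and absent at the stated ICC. If the unseen plan does specify a correction to between-ward degrees of freedom, the error rate is protected, but power is then that of the ward-level test. The statement that cluster randomisation accounts for intraclass correlation is wrong in any case.

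The figures assume equal ward sizes, a normal outcome, the stated SD of 1.8 and a two-sided test. This should be corrected before results are reported.

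**What to change.** - Sample size: replace the single ICC by a range labelled as assumed (for example 0.01 to 0.05), and restate power or expected precision with between-ward degrees of freedom.
- Design and setting: delete the claim that cluster randomisation accounts for intraclass correlation.
- Statistical analysis: fit specialty (the matching pair) as a fixed effect, use ward-level degrees of freedom, and show the ward-specific estimates.
- Interpretation: present the result as an estimate with its interval, say that it rests on two wards per arm, and do not claim superiority from a patient-level p below 0.05.

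The cost is wording and a model option. Intervals become wider and the claim weaker; no further wards or patients are needed.

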### Study outcomes

Delirium positive is defined as the occurrence of delirium assessed by a nurse researcher using the 3D-DST. Enrolled patients will be assessed twice daily for delirium by a nurse researcher using the 3D-DST for the same period of time as the nurses in the wards. Delirium duration, delirium severity, incidence of delirium, length of stay, in-hospital mortality, delirium assessment, delirium prevention, and treatment interventions performed by medical staff will be recorded by the nurse researcher.

The primary outcome of the study is delirium duration: defined as the number of delirium positive days in older adults between admission and death/transfer from the ward.

Secondary outcomes include six aspects.The severity of delirium: defined as the score of the CAM-S scale evaluated by the nurse researcher.Delirium incidence: defined as the percentage of delirium-positive patients accounting for the total number of included patients from admission to death/transfer out of the ward who were assessed by the nurse researcher using the 3D-DST.Length of stay: defined as the total number of of hospital days from admission to the day of death/transfer.Mortality rate: defined as the percentage of patients who died during hospitalization account for the total number of enrolled patients.The rate of adherence to delirium assessment: defined as the number of delirium assessments by the nurse as a percentage of the number of theoretically required assessments between patient’s admission and death/transfer out of the ward.The rate of adherence to delirium prevention and treatment: defined as the number of preventive and treatment interventions implemented by nurses and clinicians as a percentage of the number of theoretically required interventions between patient’s admission and death/transfer from the ward.

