### Trial status

Enrollment is ongoing. Recruitment has began in September 2020 and will be expected to conclude in November 2023. The target enrollment for the study is 202 participants.

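### The claimed power of more than 80% is about 22% on the plan's own inputs, and 202 patients does not follow from its incidence and drop-out figures

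*Protocol article*

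**What the plan says.** The Sample size section of the protocol article powers the trial on the primary outcome, delirium duration. Under Study outcomes this is "defined as the number of delirium positive days in older adults between admission and death/transfer from the ward".

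The inputs are:

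- effect: "We expect that the delirium duration of the intervention group will be one day shorter than that of the control group"
- spread: "with a standard deviation of 1.8"
- alpha 0.05, with sidedness not stated
- clustering: "intraclass correlation coefficient of 0.00001"

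From these it concludes: "Our study will be estimated to provide more than 80% power, at least five delirium-positive patients in each group (ward". It adds a requirement for 20 delirium-negative patients without making clear whether that is per ward, per arm or overall. It then takes an incidence of about 10% and finishes "with an estimated 10% of patients dropping out during the study, at least 202 older patients will be needed". The Trial status section repeats the total: "The target enrollment for the study is 202 participants".

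Design and setting, and Cluster randomization and blinding, fix four wards, with one neurology and one respiratory ward in each arm.

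**The concern.** Five delirium-positive patients in each of two wards is 10 per arm. The assumed effect is 1/1.8, a little over half a standard deviation, and 10 per arm is far too few to detect that with 80% power. Separately, the chain from positives to total enrolment does not arrive at 202.

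The trial is presented as a superiority trial with adequate power. If the real power is near 20%, a non-significant result is the likely outcome even when the tool works as hoped, and it would be open to being read as evidence of no effect. A significant result would carry the opposite problem: with so few patients, only estimates well above 1 day reach significance.

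**Working it through.** **Inputs.** Difference 1 day, SD 1.8, alpha 0.05, ICC 0.00001, five delirium-positive patients per ward, incidence 10%, drop-out 10% (all from Sample size); four wards, two per arm (Design and setting; Cluster randomization and blinding).

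**Clustering as stated.** The design effect is 1 + (m − 1) × ICC. With m = 5 it is 1 + 4 × 0.00001 = 1.00004. The stated ICC has no effect on the calculation, so an individual-level formula applies.

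**Attempt to reproduce the stated power.** Positives per arm are 2 × 5 = 10. The standard error of the difference is 1.8 × √(1/10 + 1/10) = 0.805, so the noncentrality is 1/0.805 = 1.242. Two-sample t-test power:

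| Delirium-positive patients per arm | Two-sided | One-sided |
|---|---|---|
| 5 (reading group as arm) | 0.12 | 0.20 |
| 9.1 (what 202 enrolled leaves) | 0.20 | 0.31 |
| 10 (five per ward) | 0.22 | 0.33 |
| 52 | 0.80 | 0.88 |

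The normal approximation at 10 per arm gives 0.24 two-sided and 0.34 one-sided. The figure above 80% is not reproduced under either test, either sidedness or either meaning of group.

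**Number needed for 80%.** The normal formula is n = 2 × 1.8² × (1.96 + 0.84)² / 1² = 50.9, so 51 per arm; the t-test needs 52 (41 if one-sided). That is 104 positives in total. At 10% incidence, 104/0.10 = 1,040 evaluable patients, and 1,040/0.9 = 1,156 enrolled.

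**What 10 per arm can detect.** With 80% power, about 2.4 days (t-test). The observed difference needed for p < 0.05, taking the SD as 1.8, is 2.101 × 0.805 = 1.69 days.

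**Attempt to reproduce 202.** Positives required: 4 × 5 = 20. Then 20/0.10 = 200, and 200/0.9 = 222.2, so 223 enrolled. Adding 10% instead of dividing by 0.9 gives 220. Neither is 202. In the other direction, 202 × 0.9 = 181.8 patients, and 181.8 × 0.10 = 18.2 positives, about 9 per arm and below the plan's own minimum of 20.

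**Sensitivity to incidence.** The Introduction cites incidences of 10% to 40%. At 40%, 202 × 0.9 × 0.40 = 72.7 positives, about 36 per arm, and power is 0.65. Even the top of that range falls short.

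**Allowance for only four wards.** The figures above use patient-level degrees of freedom. With ward-level degrees of freedom (2 unpaired, 1 paired), power at 10 positives per arm falls to about 0.12 or 0.08.

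**The case against.** The strongest reply is that the primary comparison may include every patient, with zero days for those never delirious. The outcome definition is not restricted to delirious patients, the 1-day difference is stated for one group against the other, and the paragraph asks for delirium-negative patients, who would have no role in a comparison among positives. Two versions of this can be tested.

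- **Five positive plus 20 negative per ward, 50 per arm.** Power is 0.785 two-sided and 0.87 one-sided, which is close. But the total would be 100/0.9, so 112, not 202, and 5 in 25 is 20% incidence, not 10%.
- **All 202 less drop-out, about 91 per arm.** Power would be 0.96 if a 1-day difference and SD 1.8 held across all patients. They cannot at 10% incidence. A 1-day difference in the all-patient mean needs a control mean of at least 1 day, so delirious controls average at least 1/0.10 = 10 days. With 90% of controls at zero, the control variance is at least 10² × 0.1 × 0.9 = 9, an SD of at least 3.0. Even if the intervention abolished delirium, the pooled SD would be at least √((9 + 0)/2) = 2.12, above 1.8. If instead the 1-day effect applies to delirious patients only, the all-patient difference is about 0.1 day and power at 91 per arm is about 0.07 (keeping SD 1.8 as an assumption).

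The paragraph's own step of scaling up from positives by incidence also makes sense only if positives are the patients being powered.

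What stands is that the plan never says which population the difference and SD describe, and the source of the SD is not available here. A correction should settle that first. It is also fair that the planned generalized linear mixed model is not a t-test; covariates could raise power somewhat, but not plausibly from 22% to 80%. Finally, a significant result would overstate a true 1-day effect almost always rather than by necessity, since the observed SD varies.

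**Conclusion.** The concern holds. On the stated inputs, five delirium-positive patients per ward give power of about 0.22 for a 1-day difference, not more than 0.80; the positives needed are 52 per arm, about five times the number planned. The enrolment figure is a second, smaller error: the plan's own steps give 223, and 202 leaves about 18 positives and power of about 0.20.

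This rests on the delirium-positive patients being the compared population, a two-sided test, and no loss from clustering. A one-sided test does not change the conclusion (0.33), and realistic allowance for four wards makes it worse. The all-patient reading either fails to give 202 or contradicts the stated SD and incidence. The inputs, the power and the total are all printed in the article and disagree with one another, so this is not a matter of detail left to a fuller document. It must be corrected.

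**What to change.** Rewrite the Sample size paragraph as follows.

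1. State the population to which the 1-day difference and SD 1.8 apply, and whether alpha is one- or two-sided.
2. Delete the claim of more than 80% power. If the population is delirium-positive patients, say that 202 enrolled is expected to give about 18 to 20 of them, with about 20% power for a 1-day difference and a detectable difference of about 2.4 days at 80% power, before any allowance for clustering. If another population is meant, recompute power and total from inputs that fit together.
3. Correct the drop-out step: either 200/0.9, so 223, or keep 202 and say that about 18 positives are expected. Make Trial status agree.
4. Replace the count of 20 delirium-negative patients by the figure meant. At 10% incidence, five positives per ward go with 5/0.10 − 5 = 45 negatives per ward.
5. State that the primary result will be reported as an estimate with a confidence interval, and that non-significance will not be read as absence of effect.

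The cost is protocol wording only. The target of 202 need not change, but the stated power becomes far less favourable. Keeping an 80% claim on these inputs would instead need about 1,156 enrolled.
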